### Sample Size

The primary objective of this study is to detect a difference in rates of medication errors between groups (with PedAMINES vs without PedAMINES). In our crossover pilot study conducted in a single university hospital, the rate of medication errors was 70% (14/20, 95% CI 46%-88%) without PedAMINES and 0% (0/20, 95% CI 0%-17%) with PedAMINES [14]. We aim to reproduce these results in 3 university hospitals and 3 smaller hospitals. The sample size was calculated to have a power of 90% to detect a difference of at least 30% in rates of medication error between intervention groups in both sets of hospitals (university and smaller hospitals). We consider that a difference of 30% in the rate of medication errors is sufficient to modify the practice. We assumed a rate of error of 15% with PedAMINES and 45% without PedAMINES. Since this study is a crossover, observations will be paired and a McNemar test will be used to compare the rate of errors between intervention groups. For the sample size calculation, we assumed that 5% of nurses will commit a medication error with PedAMINES but not without PedAMINES and that 35% of nurses will commit a medication error without PedAMINES but not with PedAMINES (Multimedia Appendix 2). With a 2-sided risk alpha of 0.05, the needed sample size is 43 nurses for each set of hospitals. Finally, 8 nurses per randomized group must be recruited in each participating center (16 nurses per center). To prevent a potential loss of power due to misspecification of assumptions, 10 nurses will be recruited per randomized group and per participating center (total sample size: 120 nurses).

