#### Secondary Outcomes

For TDD and TDP, the mean times will be reported with 95% CI for each arm and each study period to investigate a potential carryover effect. In case of a carryover effect, intervention arms will be compared within each study period using *t* tests for independent groups. If no carryover effect is found, data will be paired and analyzed using *t* tests for paired data.

For the primary and secondary outcomes, logistic regression analyses will be conducted to test a difference in rates of errors between university hospitals and smaller hospitals with PedAMINES and with the conventional preparation method. In a generalized estimating equation logistic regression model, an interaction between interventions and university/smaller hospitals will be tested to investigate a potential modification of the efficacy of PedAMINES in smaller hospitals compared with university hospitals. Analyses of primary and secondary outcomes will be conducted in nurses with more than 10 years of experience and in nurses with less than 10 years of experience. Means and standard deviations will be determined for stress and satisfaction scores of individuals for each questionnaire item as well as for the UTAUT questionnaire and reported with descriptive statistics. Pearson correlations will be computed between the HR measures obtained with the watch and the scenario phases for each of the preparation methods used. Data analysis will be carried out using GraphPad Prism version 6.0 (GraphPad Software, Inc) for graph figures, Stata/IC version 14 (StataCorp LLC) for descriptive analyses, and R version 2.15.2 (R Foundation) for statistical tests and 95% CI. Due to the nature of the interventions, we expect to have no missing data. In case of missing data, a complete case analysis will be conducted and no multiple imputation is planned. In order to assess interrater reliability on video reviewing, a kappa score—which provides a measure of interrater agreement independent of chance—will be calculated.

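### The GEE logistic interaction between method and hospital type has no finite estimate, and its usual robust Wald test gives a false near-zero p value, if exactly one hospital set has no PedAMINES errors

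*Protocol article*

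**What the plan says.** The Secondary Outcomes part of the statistical analysis section sets out two logistic analyses by hospital type. One is to "test a difference in rates of errors between university hospitals and smaller hospitals with PedAMINES and with the conventional preparation method". The other concerns effect modification: "In a generalized estimating equation logistic regression model, an interaction between interventions and university/smaller hospitals will be tested". The text names no test statistic (Wald, score or likelihood ratio), no standard error and no fallback for a cell without events.

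The Sample Size section gives the pilot results: "the rate of medication errors was 70% (14/20, 95% CI 46%-88%) without PedAMINES", and "0% (0/20, 95% CI 0%-17%) with PedAMINES". It then states: "We aim to reproduce these results in 3 university hospitals and 3 smaller hospitals". The calculation itself uses less extreme rates: "We assumed a rate of error of 15% with PedAMINES and 45% without PedAMINES". Recruitment is 10 nurses per randomized group and center, so 20 per center and 60 in each set of three hospitals.

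The Introduction says that even bigger improvements are expected in the smaller hospitals. The interaction is the formal model-based test of that expectation.

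**The concern.** A logistic model works on the log-odds scale, where a cell with no events sits at minus infinity. The interaction is built from four cells (two methods by two hospital types), and the two app cells may hold very few errors if the app performs as it did in the pilot.

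The failure is worse than a wide interval. In a GEE fit with the usual sandwich variance, the residuals of the empty cell shrink together with its fitted probability, so its standard error stays small while its estimate diverges. One nurse's error among 120 could then be reported as overwhelming evidence that the app works better, or worse, in one type of hospital. An ordinary logistic fit to the PedAMINES data alone fails in the opposite direction under a Wald test: the standard error explodes and a real difference is missed.

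**Working it through.** **The plan's own figure.** The discordant shares assumed are "5% of nurses will commit a medication error with PedAMINES but not without PedAMINES" and "35% of nurses will commit a medication error without PedAMINES but not with PedAMINES". So pd = 0.05 + 0.35 = 0.40 and d = 0.35 − 0.05 = 0.30. With two-sided alpha 0.05 and 90% power,

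n = [1.96 × √0.40 + 1.2816 × √(0.40 − 0.09)]² / 0.09 = 42.4, rounded up to 43.

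This reproduces the stated 43 per hospital set. The primary comparison is not in question.

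**Example with one empty cell.** Take 60 nurses per set, table errors 42/60 (the pilot's 70%) in both sets, and app errors 0/60 in one set and 1/60 in the other. Let the one nurse with an app error also have a table error. In a saturated GEE logistic model with independence working correlation, the robust variance of a cell's log odds is

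- cell with events: 1/[n p(1 − p)]
- empty cell with fitted probability μ → 0: nμ²/(nμ)² = 1/n

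The terms are:

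- two table cells: 2/(60 × 0.7 × 0.3) = 0.1587
- app cell 1/60: 60/59 = 1.0169
- app cell 0/60: 1/60 = 0.0167
- within-nurse covariance: −2 × (1 − 0.7)/[(59/60) × 12.6] = −0.0484

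The sum is 1.144, so the SE is 1.07. The fitted model returned an interaction of 22.5 with SE 1.06, which is this sum without the 1/60 term (√1.127). Hence z is about 21. The value 22.5 marks only where the iterations stopped; the true maximum is infinite.

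| Test on the same data | p |
|---|---|
| GEE, robust Wald | about 1e-99 |
| GEE, robust Wald, stopped at 10 iterations | 2.7e-11 |
| GEE, bias-reduced sandwich, Wald | about 1e-96 |
| GEE, model-based SE (about 76,000), Wald | 0.9998 |
| GEE, score test | 0.30 |
| Within-nurse differences, unequal-variance t test | 0.84 |
| Fisher's exact test, 0/60 v 1/60 | 1.0 |

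An exchangeable working correlation gave an undefined SE, or p about 1e-135 when the two sets were swapped. For the within-nurse difference (table error minus app error) the set means are 42/60 = 0.700 and 41/60 = 0.683. The difference is −1.7 percentage points (95% CI −18.5 to 15.2).

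**How often exactly one set is empty.** For a true app error rate p common to both sets, q = (1 − p)^60 is the chance that one set is empty, and 2q(1 − q) the chance that exactly one is. Type I error was simulated at nominal 5%, with a table rate of 45% in both sets. Within-nurse errors were taken as independent, which is an assumption.

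| App error rate | q | Exactly one empty set | Type I error, robust Wald |
|---|---|---|---|
| 0.5% | 0.740 | 38% | about 40% |
| 1% | 0.547 | 50% | about 50% |
| 2% | 0.298 | 42% | about 42% |
| 3% | 0.161 | 27% | about 27% |
| 5% | 0.046 | 9% | about 11% |
| 15% | 0.00006 | 0.01% | about 5% |

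The last two columns nearly coincide because every simulated trial with exactly one empty set rejected. The within-nurse difference test kept type I error between 4.5% and 5.4% at app rates from 0.5% to 15%.

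**Both sets empty.** The robust Wald p is 1.0 with table errors 42 v 42, 0.25 with 42 v 48 and 0.03 with 36 v 48. The result then reflects only the table arm, and the odds-scale effect of the app is not estimable.

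**PedAMINES-only comparison.** For 0/60 v 6/60, the logistic Wald test gives p = 0.999, the likelihood-ratio test of the same model p = 0.003 (chi-square 8.63, 1 df) and Fisher's exact test p = 0.027.

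**The case against.** The strongest reply is that the article does not commit to a robust Wald test. It says only that an interaction will be tested, and the table above shows that the answer depends on the statistic chosen. That stands, so the near-zero p value follows from common GEE practice, not from the article's words. It does not remove the concern: of the tests available within the stated model, the two Wald versions are unusable in opposite directions, and nothing in the text points to the score test. The same applies to the PedAMINES-only model, where only a Wald test gives p = 0.999.

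A reader might infer that reproducing the pilot would itself create a false finding. The figures do not support that. The pilot reproduced in both sets means two empty cells, and p is then not falsely near zero. The false result needs exactly one empty set.

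A reader might also infer that the test fails under the plan's own assumptions. It does not: at a 15% app error rate, which lies inside the pilot's confidence interval, an empty set is almost impossible. Against that, 15% is a sample-size assumption, whereas the only observed rate in the document is 0/20.

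Finally, the Primary Outcome section reports error rates, McNemar tests and differences with confidence intervals for the university and for the smaller hospitals. Anyone who sees 0/60 and 1/60 beside an enormous odds ratio should be suspicious. This limits the risk of a wrong conclusion but does not repair the test.

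**Conclusion.** The concern holds for a secondary test, within limits. The stated logistic interaction has no finite estimate when a hospital set has no app errors, and the article provides nothing in its place. With exactly one empty set, the usual robust Wald test gives a false near-zero p value. If true rates are equal in both sets, that puts type I error at roughly 27% to 50% for app error rates of 0.5% to 3%, about 11% at 5%, and the nominal level at 15%.

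These figures assume 60 nurses per set, a robust Wald test, a table error rate of 45% and independence within nurse. Results were similar at a table rate of 70%. The primary McNemar analysis and the 43 nurses per set are unaffected.

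**What to change.** Replace the interaction test. For each nurse, compute table error minus PedAMINES error (−1, 0 or 1). Compare the mean between university and smaller hospitals with an unequal-variance test, and report the difference in risk differences with its 95% CI. Within each method, compare hospital types by Fisher's exact test, with a risk difference and CI. Give odds ratios only as supportive, from a Firth-penalised fit or with a score test.

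This costs a few lines of wording and no new nurses or data. It also fits the Primary Outcome section, which already reports differences in error rates and names Fisher's test. The downside must be stated: the question moves from relative to absolute effect modification, so differing table error rates alone can produce an interaction even where the app's relative effect is the same. With no app errors in either set, the comparison reflects only the table arm, and the report should say so.

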To address these problems, we followed an evidence-based and ergonomic approach [12] to develop an innovative and customizable mobile device app called Pediatric Accurate Medication in Emergency Situations (PedAMINES). This app was designed to support nurses and physicians step-by-step from order to delivery of a wide range of drugs in real time, including those requiring continuous infusion [13]. In a previous single center simulation-based randomized controlled trial, we have shown that medication errors reduced significantly from 70% to 0% by using PedAMINES when compared with conventional methods [14]. PedAMINES also dramatically reduced TDP and TDD. The purpose of this protocol is to investigate whether the use of PedAMINES might similarly reduce medication errors, TDP, and TDD in other university hospitals and in smaller hospitals where nurses and physicians are exposed to a much lower extent to pediatric resuscitations. Simulation was used as an investigational method to assess these outcomes. We hypothesize that PedAMINES might reduce medication errors and delays to TDP and delivery independently of the existing conventional preparation methods or nurse skills. We expect even bigger improvements in smaller hospitals due to strong disparities between nurses less exposed to pediatric resuscitations.

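### Nurse experience is analysed only in separate subgroups, which cannot show whether the effect depends on experience; an interaction test is named for hospital type alone

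*Protocol article*

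**What the plan says.** Two consecutive sentences under Statistical Analysis, Secondary Outcomes, deal with possible effect modifiers, and they do so differently.

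- **Hospital type.** In a GEE logistic model, "an interaction between interventions and university/smaller hospitals will be tested".
- **Experience.** The primary and secondary outcomes are analysed "in nurses with more than 10 years of experience and in nurses with less than 10 years of experience". No interaction test is named, and the article does not say how the two sets of results will be compared, or whether they will be.

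The Introduction hypothesises that the app reduces errors and delays "independently of the existing conventional preparation methods or nurse skills".

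The article gives no expected number of nurses in either experience group. It describes randomisation as stratified but does not name experience as a factor.

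**The concern.** Whether an effect depends on experience is a question about the difference between two effects. Two separate tests each ask whether an effect exists in one group. If both are significant, that does not show the benefit is independent of experience. If only one is, that does not show the benefit depends on it, because the other group may simply be too small.

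At stake is a secondary claim: that the app works regardless of how experienced the nurse is. Experience is the only nurse-level characteristic for which the article plans an effect analysis, so readers will probably look there for evidence on the skills hypothesis. The stated method can neither support nor refute it.

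The grouping also has a gap. Strictly more and strictly less than 10 years leaves a nurse with exactly 10 years in neither group.

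**Working it through.** **Inputs, from the Sample Size section.** Error only without the app: 35% of nurses. Error only with the app: 5%. So the discordant total is pd = 0.40 and the difference is d = 0.30. Two-sided alpha is 0.05, power 90%, and the total is 120 nurses. The pilot found 70% (14/20) against 0% (0/20).

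**Inputs that are assumptions.** The split of the 120 nurses by experience, and any effect smaller than planned.

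**Step 1: reproduce the plan's figure.** n = [1.96 × √pd + 1.2816 × √(pd − d²)]² / d² = [1.96 × √0.40 + 1.2816 × √0.31]² / 0.09 = 42.39, rounded up to 43. This agrees with the article: "With a 2-sided risk alpha of 0.05, the needed sample size is 43 nurses for each set of hospitals". At n = 43, enumerated power is 93.0% for the uncorrected McNemar test and 89.2% for the exact version.

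**Step 2: power in each subgroup.** Give both groups the same true effect (35%/5%) and enumerate the McNemar test, counting significance in favour of the app.

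| Nurses in group | Uncorrected | Exact |
|---|---|---|
| 30 | 79.5% | 71.3% |
| 40 | 90.9% | 86.3% |
| 60 | 98.5% | 97.2% |
| 80 | 99.8% | 99.5% |
| 90 | 99.9% | 99.8% |

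**Step 3: chance that exactly one group is significant.** With powers P1 and P2, this is P1(1 − P2) + P2(1 − P1). For 80/40 with the exact test: 0.9951 × 0.1370 + 0.8630 × 0.0049 = 0.1405.

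| True effect, same in both groups | Split | Uncorrected | Exact |
|---|---|---|---|
| Planned (35%/5%) | 60/60 | 2.9% | 5.4% |
| Planned | 80/40 | 9.3% | 14.1% |
| Planned | 90/30 | 20.6% | 28.8% |
| 20 points (25%/5%, assumed) | 60/60 | 24.5% | 32.3% |
| 20 points (assumed) | 90/30 | 47.6% | 58.5% |
| Pilot (70%/0%) | 60/60 to 90/30 | about 0% | about 0% |

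**Step 4: benchmark.** A Wald test on the difference between the two groups' paired differences, simulated with 200,000 runs per setting and no true difference, rejected in 5.5% of runs at 60/60 and 5.9% at 90/30. Its false-positive rate hardly depends on the split or on the size of the common effect.

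**Step 5: what the interaction test can resolve.** The variance of one nurse's paired difference is pd − d² = 0.31. At 60/60 the standard error of the difference between groups is √(0.31/60 + 0.31/60) = 0.102, so the 95% CI is about ±20 percentage points (1.96 × 0.102). At 90/30 it is √(0.31/90 + 0.31/30) = 0.117, or about ±23 points. The test is valid but imprecise, so its confidence interval must be reported.

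**The case against.** The article says only that analyses will be done in each experience group. It does not say that p-values will be compared or that effect modification will be inferred, and where it wants to test modification, for hospital type, it says so. Differences in error rates are already to be reported with 95% CIs, so a descriptive reading of the experience analysis fits the text. A SAP, not at hand, may add the test. The Introduction also links skill differences to hospital type, through lower exposure in smaller hospitals, and that modifier does get an interaction test; years of experience is not stated to be the measure of skill.

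Most of this stands, and it limits the point. A reader might infer that separate testing will often produce a spurious difference between experience groups. The documents do not support that. With the protocol's own effect and an even split, discordant significance occurs in about 3-5% of trials, no more than the 5-6% of a valid interaction test, and under the pilot effect it practically never occurs. The higher figures need an uneven split or a smaller effect, and the article states neither. Cutting by experience within one hospital set would also raise the risk, but the article does not describe that cut.

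A reader might also infer that nurses with exactly 10 years are lost to the trial. They would be missing only from this split and would remain in the main and hospital-type analyses.

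What the objection does not remove is that the article fixes the factor, the cut-point, the outcomes and the separate-analysis form, and that this form cannot answer whether the effect depends on experience, whatever the split.

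**Conclusion.** The point holds in a limited form. As written, the experience analysis cannot show whether the app's effect depends on experience, while the neighbouring sentence uses a suitable method for hospital type. This does not depend on any assumption about group sizes.

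The risk of a false difference is conditional. At the planned effect it is about 3-5% at 60/60, 9-14% at 80/40 and 21-29% at 90/30. It is 25-32% at 60/60 if the true effect is only 20 points, and about 0% under the pilot effect. These ranges run from the uncorrected to the exact McNemar test, and they matter only if the two results are read as a comparison.

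The gap at exactly 10 years is a small wording defect. The point concerns a secondary analysis and leaves the primary comparison untouched. It is worth correcting because the correction is nearly free.

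**What to change.** Add an intervention-by-experience interaction test and state the method for each outcome.

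- **Error rates.** Compare the within-nurse paired difference between the two experience groups on the risk-difference scale. Alternatively use the planned GEE with a link that tolerates near-zero error rates: a logistic interaction may not be estimable if errors with the app are close to the pilot's 0/20.
- **TDP, TDD and dose deviation.** Compare the within-nurse differences between experience groups. A logistic model does not suit these continuous outcomes.
- **Subgroup results.** Report both groups' estimates with 95% CIs and label them descriptive. State that a non-significant interaction is not evidence of independence, given the width of its interval.
- **Grouping.** Define the groups as 10 years or more and less than 10 years, so that every nurse belongs to one.

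The cost is a few sentences in the plan and one more comparison per outcome. No new data are needed, provided the survey on the day of participation records experience finely enough to place a nurse at the 10-year boundary.

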
### Outcome Measures

The primary outcome of the study is the medication dosage error rate in each allocation group during the sequence from drug preparation to drug injection. A secondary outcome is the elapsed time in seconds, in each allocation group, between the oral prescription by the physician and drug delivery by the nurse. TDP completion by the nurse is included in TDD. Comparisons of medication errors and TDD between allocation groups in each hospital and between each of the 6 hospitals will be assessed as secondary outcomes. At the end of the scenario, a 4-item questionnaire using a 10-point Likert scale will be provided to the participants. The questionnaire measures (1) the overall stress perceived (On a scale of 1 to 10, how much stress did you feel during the whole resuscitation scenario?), (2) the stress perceived with PedAMINES (On a scale of 1 to 10, how much stress did you feel using PedAMINES?), (3) the stress perceived with the infusion rate table (On a scale of 1 to 10, how much stress did you feel using the infusion rate table?), and (4) the satisfaction about the preparation method used during the resuscitation scenario (On a scale of 1 to 10, how much satisfaction did you get during the resuscitation scenario with the help of PedAMINES and with the help of the infusion rate table?). A baseline heart rate (HR) before the beginning of the scenario as well as continuous HR monitoring of each participant reflecting his or her stress level will be recorded during the resuscitation scenario. Mean delta HR values (difference between HR peak values and baseline HR) will be obtained during some small segments of scenario and correlated to the scenario phases and the preparation methods used. The segments of interest are (1) when prompted to start the resuscitation because of asystole just before massage and ventilation, (2) when prompted to prepare dopamine either with PedAMINES or the infusion rate table, (3) the first 30 seconds when dopamine is being prepared, (4) the last 30 seconds when dopamine is being prepared, (5) the setting up of the pump, (6) the washout period, (7) when prompted to prepare norepinephrine either with PedAMINES or the infusion rate table, (8) the first 30 seconds when norepinephrine is being prepared, (9) the last 30 seconds when norepinephrine is being prepared, (10) at announcement of successful resuscitation achievement, and (11) 1 minute later. Acceptability and usability testing of the app will be assessed using a 52-item questionnaire based on the unified theory of acceptance and use of technology (UTAUT) model [20]. UTAUT provides a useful tool to assess the likelihood of success for new technology introductions and helps to understand the drivers of its acceptance.

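### The planned heart-rate correlations do not estimate a difference between PedAMINES and the infusion table; in addition, one heart-rate segment has no within-nurse pair and satisfaction has no score per method

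*Protocol article*

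**What the plan says.** All the material is in the Protocol article.

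- **HR measure (Outcome Measures).** Delta HR is peak minus baseline. Mean values are to be "obtained during some small segments of scenario and correlated to the scenario phases and the preparation methods used".
- **HR analysis (Statistical Analysis, Secondary Outcomes).** "Pearson correlations will be computed between the HR measures obtained with the watch and the scenario phases for each of the preparation methods used". No HR contrast between the two methods is stated.
- **Segments (Outcome Measures).** Eleven named segments are listed. The dopamine part ends with "4) the last 30 seconds when dopamine is being prepared, (5) the setting up of the pump, (6) the washout period". The norepinephrine part ends with "9) the last 30 seconds when norepinephrine is being prepared, (10) at announcement of successful resuscitation achievement, and (11) 1 minute later".
- **Questionnaire (Outcome Measures).** "a 4-item questionnaire using a 10-point Likert scale will be provided to the participants". Item 1 is overall stress, item 2 stress with PedAMINES and item 3 stress with the infusion table. Item 4 asks "how much satisfaction did you get during the resuscitation scenario with the help of PedAMINES and with the help of the infusion rate table". The analysis section plans a mean and SD for each item.

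**The concern.** In a crossover trial each nurse works with both methods, so the informative HR quantity is the within-nurse difference between them. The stated statistic instead relates HR to the phase of the scenario, separately for each method. Phase is a set of named categories, and a correlation with it describes how HR moves through the scenario. It does not say whether HR is higher with one method than with the other.

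Two details of data definition add to this. One HR segment appears for one drug only, so the crossover pairing is absent there. And stress is asked once per method, whereas satisfaction is asked once for both. At stake is whether the report can say anything about HR-measured stress or satisfaction by preparation method from the analyses as written.

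**Working it through.** The plan gives no figure for stress or satisfaction to reproduce. Its only calculated figure, 43 nurses per set of hospitals for the McNemar test, reproduces: [1.960·√0.40 + 1.282·√(0.40 − 0.30²)]² / 0.30² = 42.39, rounded up to 43. It does not enter this point.

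**1. What Pearson r responds to.** With phase code x and delta HR y, r = Sxy / √(Sxx·Syy), where each term uses deviations from the mean. Adding a constant c to every y leaves the deviations, and so r, unchanged. This is algebra and needs no assumption about the data.

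Illustration with assumed values for the three segments of one preparation (prompt, first 30 s, last 30 s), coded 1, 2, 3:

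- Method X: 20, 25, 30 bpm, mean 25. Deviations −5, 0, 5; Sxy = 10, Sxx = 2, Syy = 50; r = 10/√100 = 1.0.
- Method Y: 35, 40, 45 bpm, mean 40. Same deviations; r = 1.0.

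The methods differ by 15 bpm throughout and the two correlations are identical. The same happens with an assumed profile over all 11 segments (30, 20, 25, 30, 22, 8, 20, 25, 30, 15, 5 bpm). In time order Sxy = −142, Sxx = 110 and Syy = 738.9, so r = −142/√(110 × 738.9) = −0.50. After adding 15 bpm everywhere, r is still −0.50.

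**2. Pump set-up.** Comparing the two halves of the segment list:

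| | Dopamine | Norepinephrine |
|---|---|---|
| Prompt | 2 | 7 |
| First 30 s | 3 | 8 |
| Last 30 s | 4 | 9 |
| Pump set-up | 5 | not listed |

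Segments 2–4 and 7–9 form three matched pairs. Segment 5 has no partner. The Sample Size section gives 10 nurses per randomized group and center, and there are 6 centers: 10 × 6 = 60 nurses per sequence. Pump set-up HR therefore comes from 60 nurses with PedAMINES and another 60 with the table, with no within-nurse pair.

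The cost in precision, with equal SD σ and within-nurse correlation ρ (assumed, since the article gives none):

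- Unpaired, 60 vs 60: SE = σ√(2/60).
- Paired, 120 nurses: SE = σ√(2(1 − ρ)/120).
- Ratio = √(2/(1 − ρ)): 1.7 for ρ = 0.3, 2.0 for ρ = 0.5, 2.6 for ρ = 0.7.

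**3. Satisfaction.** Four items are counted. Three are the stress items, which leaves one for satisfaction, and its wording names both methods. One item with one mean and SD gives one number that cannot be assigned to either method. Items 2 and 3 show the same form handled separately by method for stress.

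**The case against.** Several points on the other side are fair.

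- **Perceived stress can be compared.** A reader might infer that no comparison of stress between methods is possible. The article does not support that: items 2 and 3 rate each method separately, their means and SDs are planned, and the Limitations section says the scale can be used for a difference in perceived stress. This stands.
- **These are minor outcomes.** The stated objective covers medication errors, TDP and TDD. No test or sample size depends on stress or satisfaction. This also stands and limits the weight of the point.
- **Time order is a natural code.** The phases are listed chronologically, so the dependence of r on an arbitrary numbering should not carry the argument. Agreed. The argument above holds with time-order coding.
- **Outcome Measures also mentions correlation with the methods.** A correlation of HR with a two-level method indicator would reflect a difference. But the analysis section does not state one. It states correlations with phases, within each method.
- **Segment 5 names no drug, and item 4 might be answered with two ratings.** Both are possible. The position before the washout and the count of four items make the other reading likelier, and either way the text needs to be settled.
- **HR is recorded continuously**, so the pump set-up data are not lost, and a randomized 60 vs 60 comparison remains. True. What is missing is the listed segment, and with it the pair.

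Two stronger readings are tempting but unsupported. One is that 120 × 11 = 1,320 readings will be treated as independent: the article does not say whether correlations are computed per nurse, on means or on pooled readings. The other is that peak HR will be inflated under the slower method because segments differ in length: the first and last preparation windows are fixed at 30 seconds, the length of the washout may be set in the scenario appendix, which is not shown, and any size would rest on assumed autocorrelation.

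**Conclusion.** The point holds for HR-measured stress as analysed and for satisfaction as collected, and no further. The Pearson correlations do not estimate a difference in HR between methods: a uniform difference of any size leaves r unchanged, whatever the data. The pump set-up segment, as listed, has about 60 nurses per method and no pairs, with a standard error 1.7 to 2.6 times that of the paired comparison if the within-nurse correlation lies between 0.3 and 0.7 (an assumed range). The three other preparation segments are matched. Satisfaction item 4, as written, yields one score attributable to neither method. The primary outcome and the sample size are unaffected. The change is still worth making, because the HR part can be put right from data already being recorded.

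**What to change.** 1. **HR analysis.** Replace the Pearson correlations with a within-nurse contrast of delta HR between methods on the matched segments (2–4 against 7–9). Either report paired differences by segment, taking account of period, or fit a linear mixed model with method, phase, method-by-phase, period/drug and a random nurse effect. Period and drug are the same factor here, since dopamine always comes first. Report the method difference in bpm with a 95% CI.
2. **Segments.** Add a pump set-up segment for norepinephrine, taken from the continuous recording, and name the drug in segment 5.
3. **Satisfaction.** Split item 4 into one item per method and summarise the two as for stress items 2 and 3.

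The cost is analysis wording and one extra questionnaire line. Items 1 and 2 can be applied to nurses already studied. Item 3 helps only nurses who have not yet completed the form (the article says enrollment began in March 2017). If single scores have already been collected, report them as overall satisfaction and not by method.
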